### Data collection

Data collection involves administering two surveys through Qualtrics, a secure online survey platform hosted on the University of North Carolina at Chapel Hill server. The baseline survey assessed information about the most recent therapy session and the preceding week, while the follow-up survey collected data on the subsequent therapy session and the days leading up to it (see
Table 1).

**Table 1. T1:** Measurement tools and timeline.

Domains and measures	Temporal reference	Baseline at session X	Follow-up at session X+1
*Demographic and therapy domain*			
Sociodemographic, clinical, and treatment data form	treatment epoch	✓	
*Personality domain*			
Big Five Inventory–2-Extra-Short form	trait	✓	
The Level of Personality Functioning Scale–Brief Form 2.0	trait	✓	
*Mental health state domain*			
International Positive and Negative Affect Schedule-Short Form	state–session	✓	
Patient Health Questionnaire–9	state–session	✓	
Generalized Anxiety Disorder–7	state–session	✓	
Single-item global measures of symptom severity, psychosocial functioning, and quality of life	state–session	✓	✓
*Therapeutic relationship domain*			
Real Relationship Inventory–Client form	current relation	✓	
Working Alliance Inventory–Short Revised	state–session	✓	✓
Patient Session Questionnaire	state–session	✓	✓
in-Session Patient Affective Reactions Questionnaire	state–session	✓	✓
Rift In-Session Questionnaire	state–session	✓	✓
*Session outcome domain*			
Session Evaluation Scale	outcome–session	✓	✓

### Measures

This study employs a comprehensive battery of measures to collect a wide array of data related to the therapeutic process and patient factors. The demographic and therapy domain of the patient encompasses the sociodemographic details of the patient and the psychotherapy details. The personality domain refers to measures of personality trait characteristics. The mental health state domain refers to the traditional measures of symptoms that currently affect the participants day to day life. The therapeutic relationship domain will evaluate specific elements of the in-session relationship between the patient and the therapist. The session outcome domain will assess the quality of the therapy session from the patient’s perspective.

### Data form domain

**
*Sociodemographic, Clinical, and Treatment Data Form.*
** This form captures self-reported information on the patient’s age, biological sex, gender identity, educational background, ethnicity, any existing psychiatric diagnoses, and the duration and frequency of the current psychotherapeutic intervention. It also records the modality of session attendance (i.e., in-person, video call, or telephone call), the setting of therapy (for example, private practice, private healthcare institution, university counseling center), and the biological sex of the therapist. Information about the specific types of psychotherapy that participants were undergoing was not gathered.

**
*Personality domain.*
** The
*Big Five Inventory–2-Extra-Short form* (BFI-2-XS) (
Soto & John, 2017) is a concise 15-item self-report instrument that captures personality at the level of the Big Five domains. Each domain is represented by three items, and each item is rated on a 5-point Likert scale. The five domains include extraversion, agreeableness, conscientiousness, negative emotionality (also referred to as neuroticism), and open-mindedness. The average alpha reliability for the BFI-2-XS domain scales fell between .61 and .63, with the total range extending from .51 to .72. Test-retest reliabilities for these scales averaged .70 in the university sample (ranging from .60 to .80) and .76 in the college sample (with a range of .71 to .80).

The
*Level of Personality Functioning Scale-Brief Form 2.0* (LPFS-BF 2.0) (
Weekers *et al.,* 2019) is a 12-item self-report questionnaire used to assess the severity of personality pathology. It measures impairment in self-functioning and interpersonal functioning based on levels of personality functioning according to the DSM-5. Cronbach’s alpha for the LPFS-BF 2.0 was .82 for the total scale, .79 for the self-functioning scale, and .71 for the interpersonal functioning scale.

**
*Mental health state domain.*
** The
*International Positive and Negative Affect Schedule–Short Form* (I-PANAS-SF) (
Thompson, 2007) is a 10-item self-report measure that captures the frequency of positive and negative affects experienced over the past week. It provides an understanding of the emotional states of the patients. The I-PANAS-SF positive affects and negative affects subscales showed Cronbach’s alphas of, respectively, .78 and .76.

The
*Patient Health Questionnaire–9* (PHQ-9) (
Kroenke *et al.*, 2001) is a depression screening tool that captures the severity of depressive symptoms over the past 7 days. It can be used to evaluate symptoms according to the DSM-5 criteria. The internal reliability of the PHQ-9 in the primary care sample was Cronbach’s alpha of .89.

The
*Generalized Anxiety Disorder–7* (GAD-7) (
Spitzer *et al*., 2006) is a 7-item self-report measure of anxiety symptoms, with a focus on generalized anxiety disorder. It captures the severity and frequency of anxiety symptoms over the past 7 days. The internal consistency of the GAD-7 was Cronbach’s alpha of .92.

The three
*Single-item global measures of symptom severity, psychosocial functioning, and quality of life* (SI) originally developed by Zimmerman
*et al.* (
Zimmerman *et al.*, 2006) were used in this study with adaptations. Specifically, “symptoms of depression” was replaced with “symptoms for which you are in psychotherapeutic treatment.” The symptom severity scale uses a 5-point Likert scale ranging from 0 (
*None*) to 4 (
*Severe*). The psychosocial functioning scale similarly uses a 5-point scale from 0 (
*Not at all*) to 4 (
*Extremely*). The quality of life scale ranges from 0 (
*Very good, my life could hardly be better*) to 4 (
*Very bad, my life could hardly be worse*).

**
*Therapeutic relationship domain.*
** The
*Real Relationship Inventory–Client* (RRI-C)
*form* (
Kelley *et al.*, 2010) is a 24-item self-report instrument that assesses the strength of the “real relationship.” The construct of “real relationship” is defined as “the personal relationship existing between two or more people as reflected in the degree to which each is genuine with the other and perceives the other in ways that befit the other” (
Gelso, 2009, pp. 254–255 ). The depth of this relationship hinges on both the intensity and the nature—ranging from positive to negative—of its two primary components: realism and genuineness. Realism is defined as the extent to which an individual perceives another in a truthful manner, while genuineness involves the authenticity one shows towards another and the degree to which an individual remains true to oneself (
Gelso *et al.*, 2012). It is important to acknowledge that genuineness also encompasses the personal attributes of each individual involved and the overall quality of their interaction (
Gelso, 2009). Therefore, the RRI-C includes two subscales: Genuineness and Realism. Internal consistency estimates Cronbach’s alpha for the RRI-C were .95 for the total score, .91 for the Genuineness subscale, and .90 for Realism subscale.

The
*Working Alliance Inventory–Short Revised* (WAI-SR) (
Hatcher & Gillaspy, 2006) is a succinct self-report instrument consisting of 12 items to assess the quality of the therapeutic alliance. The measure was originally developed by selecting items that accurately reflect patients’ perceptions and attitudes during therapy delineated in
Edward Bordin’s (1979) theoretical framework of the therapeutic alliance. Bordin posits that the working alliance is a collaborative and negotiated aspect of the treatment relationship, which includes three essential components: (a) mutual agreement between the patient and therapist on the therapy’s objectives; (b) the patient’s agreement with the therapist that the tasks of the therapy will address their specific issues; and (c) the quality of the interpersonal bond between the patient and the therapist. The WAI-SR is divided into three subscales, each with four items, which focus on agreement on therapy tasks, goals, and the development of an emotional bond between the patient and the therapist. With a 6-point Likert scale, it quantifies the degree of agreement, with higher scores indicating a more robust therapeutic alliance. The alpha reliabilities for all WAI-SR subscales spanned a range of .85 to .90, while the total score alpha reliabilities were recorded at .91 and .92.

Part B of the
*Patient Session Questionnaire* (PSQ) (
Samstag *et al.*, 1998) is a four-item self-report instrument measuring therapeutic alliance ruptures and their resolution during the most recent session. A rupture in the therapeutic alliance occurs when there is disagreement between the patient and therapist concerning therapy goals, diminished cooperation on therapeutic tasks, or tension within the emotional connection (
Eubanks *et al.*, 2018). While the term rupture might suggest a severe disruption in the therapeutic relationship, research often identifies even slight tensions and minor misunderstandings as indicative of such ruptures (
Eubanks *et al.*, 2018). A rupture is considered repaired or resolved when the patient and therapist successfully reestablish their collaborative efforts in therapy and reinforce their emotional connection. The part B of the PSQ includes an initial item that investigates the presence (“Yes” or “No”) of any tension, conflict, or misunderstanding in the therapist-client relationship during the session. If such an event occurred, it is followed by three items that gauge the peak intensity of the tension, the degree to which the problem was addressed in that session, and the patient’s perception of the solution of the problem by the end of the session.

The
*in-Session Patient Affective Reactions Questionnaire* (SPARQ) (
Stefana *et al.*, 2023b) is a patient-reported tool that comprises 8 items that explore the patterns of thought, feeling, and behavior activated and experienced by the patients toward their therapist during a session. It consists of two scales: Positive Affect and Negative Affect. The positive affect scale exhibited a Cronbach’s alpha coefficient of .86 and an average inter-item correlation of .61. On the other hand, the negative affect scale demonstrated an alpha of .74 and an average inter-item correlation of .41.

The
*Rift In-Session Questionnaire* (RISQ) (
Stefana *et al.*, 2023b) is a 4-item self-report questionnaire designed to measure the patient’s risk of experiencing ruptures in the therapeutic relationship. The RISQ measures feelings of belittlement, rejection, disparagement, and attack. The RISQ demonstrated good internal consistency with a Cronbach’s alpha coefficient of .75 and an average inter-item correlation of .43.

**
*Session outcome domain.*
** The
*Session Evaluation Scale* (SES) (
Lent *et al.*, 2006), part of the Helping Skills Measure (
Hill & Kellems, 2002), evaluates the quality of the therapy session from the patient’s perspective. It consists of five items, four of which are rated on a 5-point Likert scale, and the fifth item gauges the effectiveness of the session. The 5-item SES showed a Cronbach’s alpha coefficients ranging from .88 to .89 (
Lent *et al.*, 2006).

### Efforts to minimize potential sources of bias

In this study, comprehensive measures were implemented to address potential biases. First, to ensure a representative sample, participants were recruited through ResearchMatch, a national online platform with a wide and diverse volunteer base across the United States. This strategy mitigates selection bias and improves the generalizability of the study. Second, we adopted a gender-sensitive approach, emphasizing non-binary gender as a pivotal variable in both analyses and interpretation of the results, ensuring more robust scientific quality and clinical relevance. Third, our longitudinal design, capturing data at two distinct time points, serves dual purposes: validating the SPARQ and RISQ, and examining score stability over time, thus reducing temporal biases. Fourth, our comprehensive set of measures encompasses various therapeutic and patient factors, ranging from sociodemographics to personality traits, reducing measurement bias by offering a holistic view of the therapeutic context. All data are collected through Qualtrics, a secure online platform that preserves participant confidentiality and minimizes response biases. Lastly, meticulous sample size estimations were made, accounting for attrition and ensuring statistical power, thereby preventing biases from under-powered analyses or inadequate representation.

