### Study objectives

This study has two primary objectives:

a. To validate the
*in-Session Patient Affective Reactions Questionnaire* (SPARQ) and the
*Rift In Session Questionnaire* (RISQ) devised by
Stefana *et al.* (2023b). These self-report measures assess the subjective affective reactions of patients toward their psychotherapists during specific therapy sessions. The study aims to establish the reliability and validity of these measures through a rigorous psychometric evaluation.b. To explore the relationships and dynamics among four elements of the therapeutic relationship: patient reactions toward the therapist, working alliance, alliance ruptures and repairs, and the real relationship. The study aims to investigate how these elements interrelate and how they collectively influence the outcomes of the therapy session, from the patient’s perspective. Furthermore, the study aims to examine possible moderating effects of patient, therapist, and process characteristics on the strength of the therapeutic relationship and the outcome of the session.

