## Methods

### Study design

This study employed a nonrandomized, two-time point longitudinal design. The study started in March 2023 and is ongoing. The initial development of the scales in
Stefana *et al.* (2023b) used a large initial item pool and a large, single administration sample to generate adequate sample size to use exploratory and confirmatory factor analysis and item response theory to guide item selection. A limitation of that work was that the SPARQ and RISQ items were originally embedded in a larger item pool. It is possible that the items would perform differently in the shorter, extracted format that would be more useful in clinical practice and therapy research. A second limitation is that each participant responded only once, so it was not possible to estimate score stability or sensitivity to change. The approach used in the present study addresses both limitations of the prior work: (a) it collects cross-sectional data for the validation of the SPARQ and the RISQ in the extracted, brief item sets, and (b) gathers longitudinal data to examine how specific elements of the therapeutic relationship are related to each other and to the outcome of the therapy session, from the perspective of patients. Furthermore, it allows us to test the moderating role of personality characteristics of the patients.

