### Data analysis

Regarding the first objective, the analysis plan for validating the two scales includes several statistical techniques to evaluate the psychometric properties. In the initial stage, will be used to evaluate the suitability of the proposed factor models on the complete sample of participants. These will use the same analytic methods used in the original scale development, but with the extracted, short-form subset of items (versus the prior work, where these items were embedded in the larger original item set). Specifically, a two-factor model representing positive affect and negative affect will be tested for the SPARQ, while a single-factor model will be applied to the RISQ (
Stefana *et al.*, 2023b). Item response theory (IRT) models will be used to analyze the options characteristics of each scale and obtain detailed information at the item level (including item difficulty, discrimination, and category functioning). In addition to these specific analyzes, several statistical procedures will be conducted to evaluate the psychometric properties of the scales. Internal consistency will be assessed using Cronbach’s alpha (for comparability with what is most often reported for other scales), McDonald’s omega total coefficients (which is more appropriate for measures that include more than one factor), and average inter-item
*r* (which avoids confounding internal consistency and scale length, which is a well-known limitation of Cronbach’s alpha;
Streiner *et al.*, 2015).

Criterion validity will be examined by calculating the correlations between the scales and various external variables, including sociodemographic, clinical, and treatment variables. Validated measures of traits, mental state characteristics, specific elements of the therapeutic relationship, and session outcomes will also be included in the analysis. Fisher’s z transformation will be used to average pooled correlation matrices, providing descriptive summaries for associations with sets of variables.

Regarding the second aim, correlations will quantify the pre-post stability of the repeated measures. The PROCESS macros will test for mediation of pre-post symptom severity, psychosocial functioning, and quality of life by ratings of the client-therapist relationship, affect, and working alliance, as well as the extent to which these might show moderated mediation due to demographic or personality variables (

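### The new scales and all their scale criteria come from one patient in one survey; plain correlations leave shared mood or halo in the validity evidence, and the platform does not remove it

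*Protocol article*

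**What the plan says.** All places are in the Protocol article.

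- *Study objectives* defines what the new scales should capture: "These self-report measures assess the subjective affective reactions of patients toward their psychotherapists during specific therapy sessions".
- *Study design* says of the present study that "it collects cross-sectional data for the validation of the SPARQ and the RISQ in the extracted, brief item sets".
- Table 1 under *Data collection* places every measure in the baseline survey. WAI-SR, PSQ, SPARQ, RISQ, SES and the three single items are repeated at follow-up; RRI-C, I-PANAS-SF, PHQ-9, GAD-7 and the personality scales are not.
- The measure descriptions under *Data form domain* show that the patient is the source throughout. The WAI-SR "is a succinct self-report instrument consisting of 12 items to assess the quality of the therapeutic alliance". The SES "evaluates the quality of the therapy session" as the patient sees it. Of the demographic and treatment form, the text says "This form captures self-reported information on the patient".
- *Data analysis* states: "Criterion validity will be examined by calculating the correlations between the scales and various external variables". Traits, mental state, relationship elements and session outcome are all among those variables. No adjustment is stated.
- *Efforts to minimize potential sources of bias* calls Qualtrics "a secure online platform that preserves participant confidentiality and minimizes response biases" and credits the breadth of the battery with "reducing measurement bias by offering a holistic view of the therapeutic context". It does not mention bias from a shared rater or a shared occasion.

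**The concern.** SPARQ has positive and negative affect scales, and RISQ asks about feeling put down, rejected or attacked. The obvious rival explanation for their correlations with alliance, rupture and session rating is general affect: a patient who feels bad may rate the therapist, the alliance and the session lower together. Halo works the same way. A zero-order correlation contains this shared part along with any reaction specific to the therapist.

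The claim at stake is specificity, that the scales measure affect directed at the therapist. The bias section suggests that response bias has been dealt with by the platform and the wide battery. Neither acts on this source. A platform does not change what one respondent carries from scale to scale, and more scales from the same rater share that rater.

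**Working it through.** The plan gives no figure on this point, so there is none to reproduce. What follows sets the text side by side and then illustrates size.

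**1. Source and occasion.** The new scales (SPARQ, RISQ) and the scale criteria (WAI-SR, PSQ, RRI-C, SES, I-PANAS-SF, PHQ-9, GAD-7) have the same rater and the same baseline survey. No therapist, observer or record-based criterion is listed. Age, sex, setting and session frequency are also correlates; they are largely factual and much less open to mood.

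**2. Critical correlation.** Inputs: N of about 700 (expected) and 315 (recommended), from *Sample size estimation*; alpha .01 two-tailed, from *Data analysis*. Formula: r = t / √(N − 2 + t²).

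- N = 700: t = 2.583, so r = 2.583 / √(698 + 6.67) = .097.
- N = 315: t = 2.592, so r = 2.592 / √(313 + 6.72) = .145.

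**3. Spurious correlation with no true association.** Assumption: each of two scales loads λ on one shared mood or halo factor and shares nothing else. Then |r| = λ². Chance of significance by Fisher z: Φ(atanh(|r|)·√(N − 3) − 2.576).

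| λ (assumed) | spurious \|r\| | P(significant), N = 700 | P(significant), N = 315 |
|---|---|---|---|
| .3 | .09 | 42% | 16% |
| .4 | .16 | 95% | 61% |
| .5 | .25 | over 99% | 97% |

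For λ = .4 and N = 700: atanh(.16) = .1614; .1614 × √697 = 4.26; 4.26 − 2.576 = 1.685; Φ(1.685) = .954.

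**4. Inflation of a real association.** Let m be the share of each score's variance due to the shared factor. Observed |r| = r_true·√((rel₁ − m)(rel₂ − m)) + m. Inputs: rel₁ = .75 (the RISQ alpha given under *Data form domain*); rel₂ = .90 and r_true = .30 (both assumed).

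- m = 0: .30 × √(.75 × .90) = .25.
- m = .10: .30 × √(.65 × .80) + .10 = .32.
- m = .20: .30 × √(.55 × .70) + .20 = .39.

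**5. Direction.** The formulas are in absolute value because SPARQ negative affect and RISQ should correlate negatively with WAI-SR and SES. Mood and halo push in that expected direction. Acquiescence adds positive covariance and would shrink those negative correlations, so it is not counted as a source of inflation for them.

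**6. What partialling can do.** Take λ = .4 and suppose that the I-PANAS-SF negative scale measures the shared mood with reliability .76 (the alpha quoted in the article). Each scale then correlates .4 × √.76 with it, and the product of the two correlations is .16 × .76 = .122. The partial correlation is (.16 − .122) / (1 − .122) = .04. Most of the spurious .16 goes, provided that I-PANAS-SF does index the shared mood.

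**The case against.** The strongest reply has five parts.

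- **The patient's view is the construct.** No outside rater can directly observe a patient's subjective reactions. This stands: self-report is not the fault.
- **The planned correlations already carry discriminant evidence.** A scale that reflected only general mood should track I-PANAS-SF, PHQ-9, GAD-7 and negative emotionality at least as strongly as alliance or session rating. This stands in part. A reader might infer that the analysis cannot separate the two at all, and that goes too far. But listing the mood correlations beside the others does not show how much of the alliance correlation survives once affect is removed.
- **No rule makes significance the test of validity.** This stands. A reader might infer from the table above that a mood-only scale would be declared valid. The article states no such rule, and an r of .09 or .16 is weak validity evidence whatever its p-value. The loadings are assumed.
- **Partialling for I-PANAS-SF is imperfect.** It covers the past week, not mood at the time of answering. That week may include the session, and it does not capture halo. This stands, and it is why the partial value should not become the sole basis of the claim.
- **An article condenses, and a fuller plan may add adjusted or lagged correlations.** The article does plan longitudinal work on how relationship elements relate to session outcome. This stands for the missing detail. It does not cover the platform statement, which is wrong as written.

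Three other readings lack support. The text does not say that the survey is completed in one sitting. Blinding has no meaning in a survey without arms. Not every scale refers to the session: the measure descriptions give I-PANAS-SF, PHQ-9 and GAD-7 a past-week window, and Table 1 gives RRI-C the current relationship.

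**Conclusion.** The point holds in a limited form. Same rater, same survey and correlations with no stated control for general affect mean that shared mood or halo can inflate the correlations with alliance, rupture and session rating. The sentence crediting the platform does not address this and claims more than a platform can deliver.

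The size is unknown because the documents give no figure for shared variance. Over assumed loadings of .3 to .5, the spurious |r| is .09 to .25. With a true correlation of .30 and the reliabilities above, an observed .25 would read as .32 to .39 at 10% to 20% shared variance. The range assumes one shared factor that acts equally on both scales.

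This does not show that SPARQ or RISQ is invalid, or that the design is unsuited to its aim. It is a wrong bias statement together with a check that costs little and bears directly on the claimed construct.

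**What to change.** 1. In *Data analysis*, report each correlation of SPARQ and RISQ with WAI-SR, PSQ, RRI-C and SES twice: raw, and partialled for baseline I-PANAS-SF positive and negative affect. Read the pair together. Use BFI-2-XS negative emotionality only as a sensitivity check, since the article reports domain alphas of .51 to .72.
2. Add correlations of SPARQ and RISQ at session X with WAI-SR, PSQ and SES at session X+1. State that these remove same-occasion variance but not a stable response style. At the 70% follow-up the article assumes, 700 × .70 = 490 patients would contribute; at the article's planning figure of 500 the critical r is .115.
3. In *Efforts to minimize potential sources of bias*, limit the Qualtrics sentence to confidentiality, drop the suggestion that a broad battery reduces measurement bias, and name shared-source (common-method) variance as a limitation.

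**Cost.** A few extra columns and no new data. Partialling may remove some true therapist-directed affect, so the partial figures are likely conservative; showing both limits the harm. *Study status* says that data collection is complete and two outputs are published, so the added analyses should be labelled as post hoc unless an earlier plan already contains them.

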### Participants

This research focuses on adults (18 years and above) receiving individual psychotherapy for a range of mental health conditions, without limiting the type of mental disorder. Participants must be fluent in English and capable of providing informed consent.

Participants are recruited through two online recruitment platforms: Research for Me and ResearchMatch. Research for Me has approximately 12,000 registered volunteers in North Carolina, while ResearchMatch (
Harris *et al.*, 2012) provides access to more than 155,000 volunteers across the United States. These platforms connect researchers with individuals interested in contributing to scientific advancements in various fields. The use of the extensive reach and user-friendly interfaces of Research for Me and ResearchMatch improves participant recruitment for this study, ensuring a representative sample from diverse backgrounds and geographic locations.

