### Sample size estimation

The study includes two main goals, and the necessary sample size varies accordingly.

The first goal is validation of the psychometrics of the SPARQ and RISQ in their brief, extracted item sets. Based on the number of items in the measures to be validated (
*k* = 8 for the SPARQ and
*k* = 4 for the RISQ), as well as the expected moderate to strong factor loadings (as found in the embedded format study;
Stefana *et al.*, 2023b), a sample size of
*N* = 315 is recommended (
Dimitrov, 2012). This sample size also accounts for the complexities of a two-factor model which includes non-normal indicators and potential missing values (
Dimitrov, 2012). However, we anticipate recruiting at ~700 participants. The sample size considered for this study is deemed feasible based on the previous psychotherapy-related study of our team that successfully used the same two online recruitment platforms.

For the second goal, evaluating prospective associations among scores rated over the course of treatment, and the potential moderating effects of personality, even using conservative estimates that only 70% of cases would complete the follow-up ratings, power would be 80% to detect effects as small as
*f
^2^
* = .02 (alpha = .01, two-tailed,
*N* = 500, and including up to 9 predictors or covariates) (
Faul *et al.*, 2009), corresponding to a small effect size using Cohen’s (
Cohen, 2013) benchmarks.

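### The article credits volunteer-registry recruitment with a representative sample and an attrition-adjusted sample size with preventing poor representation; neither can do this, and selective non-return could modestly weaken some aim 2 estimates

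*Protocol article*

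**What the plan says.** **Recruitment.** Under Participants, the two online platforms are described as "ensuring a representative sample from diverse backgrounds and geographic locations". The same section describes the pool: "These platforms connect researchers with individuals interested in contributing to scientific advancements in various fields". Under Efforts to minimize potential sources of bias the claim returns: "First, to ensure a representative sample, participants were recruited through ResearchMatch, a national online platform with a wide and diverse volunteer base", followed by "This strategy mitigates selection bias and improves the generalizability of the study".

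**Sample size.** The bias section closes by saying that "meticulous sample size estimations were made, accounting for attrition and ensuring statistical power, thereby preventing biases from under-powered analyses or inadequate representation". The allowance behind this is in Sample size estimation. About 700 participants are anticipated, and aim 2 is powered on N = 500, using what the article calls a conservative estimate that "only 70% of cases would complete the follow-up ratings".

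**Analysis.** For aim 2, Data analysis plans correlations for the stability of repeated measures, and adds: "The PROCESS macros will test for mediation" of pre-post symptom severity, functioning and quality of life. It does not say how participants without follow-up enter these analyses. For aim 1, the factor models are to be fitted on the full sample, and Study design describes the validation data as cross-sectional.

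**The concern.** Three different things are treated as one. A larger N reduces sampling error. It does not change which people join a volunteer registry, and it does not change which of them return for the second survey. A reader who takes the bias section at face value would conclude that selection and attrition have been dealt with by design.

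Attrition needs attention in this study because the second survey concerns the next therapy session (Table 1, session X+1), while the constructs of interest are alliance, ruptures and affect toward the therapist. It is plausible, though nothing in the article shows it, that patients with a poorer relationship are less likely to have or report on that session. Loss of that kind trims one end of the scales being studied. Separately, the representativeness wording would support conclusions about psychotherapy patients in general, which a volunteer-registry sample cannot support.

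**Working it through.** **1. The plan's attrition allowance.** Inputs from Sample size estimation: about 700 enrolled, 70% completing.
- Completers: 700 × 0.70 = 490, within 2% of the stated 500.
- Exactly 500 completers would need 500 / 0.70 = 714.3, so 715 enrolled.

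The allowance therefore reproduces, approximately, as a headcount. Nothing in it refers to the characteristics of those lost. The 80% power attached to N = 500 is a separate matter on which this point does not rest. For one coefficient among 9 predictors (noncentral F, noncentrality 0.02 × 500 = 10, df 1 and 490, alpha .01 two-tailed) I obtain 71.8%.

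**2. Does a larger N remove the bias?** Simulation with assumptions not in the article: true baseline–follow-up r and slope 0.50, about 30% loss, logistic return with log-odds 1 per SD.

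| Return depends on | r | slope | shift in follow-up mean (SD) |
|---|---|---|---|
| nothing (random) | .50 | .50 | 0 |
| baseline score | .47 | .50 | +0.13 |
| follow-up score | .47 | .445 | +0.26 |

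To rounding, the results are the same at N = 700, 7,000 and 70,000. Sample size does not act on this bias.

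**3. Size of the effect on aim 2 if only completers are analysed.** Assumptions: normal scores, 30% loss, return depending on the baseline relationship score M with log-odds b per SD. Let v be the variance of M among returners relative to everyone (by numerical integration).
- Path a from a baseline predictor into M, true value -.30: a′ = -.30v / (1 − .09 + .09v).
- Stability correlation, true value .60: r′ = .60√v / √(1 − .36 + .36v).

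| b | v | a′ | r′ |
|---|---|---|---|
| 0.5 | 0.954 | -.287 | .591 |
| 0.8 | 0.899 | -.272 | .580 |
| 1.2 | 0.823 | -.251 | .563 |

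Example, b = 0.8: a′ = -.30 × 0.899 / (0.91 + 0.081) = -.272, a loss of about 9%. Two-million-draw simulations agree (-.271 to -.273 and .579 to .580).

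**4. What does not move.** In the b = 0.8 simulation, with an assumed mediator-to-outcome path of -.30 and direct effect of .50, completers give about -.30 and .50. Both are unbiased, because selection acts only through a variable already in that model. The retest slope also stays at .60. Aim 1 uses baseline data from the complete sample, so loss at follow-up does not reach it.

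**5. Skewed scores.** With floor-type scores the attenuation is larger. One assumed shape gave r = .45 falling to .39 (b = 0.5) or .36 (b = 0.8). Another gave .47 falling to .41 or .39. That is a reduction of roughly 12 to 20%. The article does not give the RISQ distribution, so these figures are illustrative only.

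**6. Representativeness.** By the article's own description, both platforms reach people interested in contributing to research. Their size (about 12,000 and more than 155,000 registrants) describes reach and says nothing about similarity to non-registrants.

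**The case against.** The strongest reply is that this is mainly a matter of wording and that the article is more careful than it may seem. On recruitment it says selection bias is mitigated, not prevented. On sample size it never uses the term attrition bias. The 70% is a conservative planning figure, not a forecast of 30% loss. English fluency and being in current therapy define the eligible population, so they do not make the sample unrepresentative of it. All of this stands. What remains is that securing a representative sample is stated as an achievement in one section and as the purpose of recruitment in another, and that inadequate representation is said to be prevented by sample-size work.

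A reader might infer that PROCESS will discard about 210 of 700 baseline records (700 − 490), and that those lost are the patients with the poorest sessions. The document supports neither step. It does not state complete-case handling. N = 500 is a power input, not a definition of the analysis set, and imputation before PROCESS is not excluded. Missing-data rules may well sit in a fuller plan, so their absence from an article is not a fault. Nor does any section say who fails to return.

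A reader might also infer that the main associations are badly distorted. Under the assumptions above the bias is modest for normal scores and confined to stability correlations and the path into a baseline mediator. The larger figures depend on an assumed skew.

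**Conclusion.** The concern holds in a limited form. Two statements are wrong: volunteer registries do not secure a representative sample, and allowing for loss in N protects precision only. The analytic consequence is conditional. It requires that aim 2 is analysed on completers, which the power basis and the choice of PROCESS suggest but do not establish, and that return depends on the baseline relationship score. It also applies to mediators measured at baseline. Under those conditions, with 30% loss and log-odds of 0.8 per SD, -.30 becomes about -.27 and .60 becomes .58, with possibly more for skewed scores such as the RISQ. The mediator-to-outcome path, the direct effect and the aim 1 validation are unaffected. If return depends instead on the follow-up score itself, regression slopes are biased as well (.50 to .445 in the illustration above). The point is worth correcting because it narrows what the study may conclude and the remedy is cheap. It does not invalidate the design.

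**What to change.** 1. **Wording.** Under Participants and in the bias section, remove the claims that recruitment ensures a representative sample and that sample-size estimation prevents bias. State instead that N allows for loss of precision only, and that results apply to English-fluent registry volunteers in ongoing individual therapy.
2. **Analysis.** Estimate the aim 2 mediation models and the stability correlations by FIML or multiple imputation, with baseline SPARQ, RISQ, PSQ, WAI-SR, SES, PHQ-9 and GAD-7 as auxiliary variables. This keeps all of the roughly 700 records for paths between baseline variables. Keep complete-case PROCESS results as a sensitivity analysis.
3. **Description.** Compare returners with non-returners on the same baseline scores, all of which Table 1 shows are collected.

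**Cost.** Slightly more analysis work and a narrower generalisability statement. Study status reports that data collection is complete, and no new data are needed. **Limit.** FIML and imputation reduce bias from loss related to observed scores. They give no protection against loss that depends on unobserved events after baseline, such as leaving therapy following a later rupture, and the report should say so.
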